#### Additional evaluation

At the beginning of the intervention, we will randomly select three cases from the experimental group with needs for slight vs. moderate vs. complex care, and match them with three cases from the control group according to relevant baseline characteristics and baseline assessment scores (e.g. diagnoses, sex, age, functional health, depression). At the end of the intervention, blinded physicians will retrospectively carry out a full chart review for all six cases, based on information from the patients’ general practitioners, in order to compare the one-year periods of care management and to gain a deeper understanding of procedures and decisions of care and how enhanced coordination might change care management. For the three experimental cases, we will additionally video-record the CCM sessions 3 and 7 (monitoring and closing contacts). After the blinded physician has completed the review of these six cases, he/she will be “unblinded” and will additionally assess the videos and the CCM documentation of the three experimental cases. Later, during the dissemination phase, these videos will be used for the training and qualification of routine care CCMs.

In addition, three participants of the experimental group will be separately selected at random and asked about their perceived quality of care using the method of open in-depth interviews and qualitative content analysis.

#### Recruitment of participants

Based on the annual statistics of the emergency department of the Medical Center – University of Freiburg, the access to the target population is estimated as follows: 42,000 patients per year present at the emergency department; of these, 11,000 persons are aged 65 or older, of whom 2500 presented with chronic or geriatric diseases and were locally resident in 2015. We expect that a quarter of these patients (approx. 600) will have eligible ISAR scores and will provide informed consent and that about 20% will drop out before the 12-month follow up, resulting in approximately 480 patients. As external assessors, our experienced geriatric staff are familiar with routine care procedures and will ensure that study activities neither drain department resources nor hinder usual care processes. In summary, we are well positioned not only to ensure adequate recruitment, but also to overcome any concerns of staff regarding participation in the study and to avoid recruitment bias due to implicit resistance.

#### Assignment and randomisation

After obtaining written consent from participating patients, external assessors responsible for the screening will send contact details of the patient, relatives as well as the baseline assessment to the primary coordinating centre. There, the allocation of the patients to the study arms will be performed. Participating patients will receive a pseudonymised code and will then be assigned to the intervention or control group according to a computer-generated randomisation schedule by a study coordinator not involved in assessment or intervention procedures. Block randomisation will be used with no stratification. After assignment to the intervention or control group, the pseudonymised patient identifiers and the baseline assessment will be sent to the study centres responsible for the data management. The study site responsible for the implementation of the intervention will receive names and contact details of the patients in the intervention group in order to begin the intervention process.

#### Blinding

In both groups, patient outcomes will be collected by independent assessors to prevent the contamination of the CCM by patient assessment. Due to the pseudonymisation process, the statistician will analyse the primary and secondary outcome data without knowledge of the subjects’ allocation to the study arms. For additional qualitative analysis of CCM data in the experimental group, this kind of blinding is not possible. Due to the nature of the intervention, participants and CCM will not be blinded to the type of intervention.

### Statistical analyses

The statistician will perform an intention-to-treat and per-protocol analysis of the outcome assessment scores at baseline and 12- and 18-month follow-up (dependent variables), adjusting for baseline group differences (independent variables). The hypotheses claim superiority of the intervention group over the control group with respect to the two outcomes (functional health (WHODAS) and depression (PHQ-9)) at 12- and 18-month follow-up. As we will use a composite endpoint of the two primary outcomes (sum of z-score normed component measures), no adjustment of the significance level is necessary. Subgroup analysis will be conducted to reveal group differences in intervention effects between patients with serious versus slight health-related strain. Groups will be classified by an ISAR score of > = 3 versus < 3. Furthermore, secondary outcomes (satisfaction with care, resource utilisation, medication appropriateness) will be analysed. The assumption of ´missing at random` is assumed for the problem of missing data. The fully conditional specification method (an iterative Markov chain Monte Carlo method) will be applied for the imputation of missing data. Dropout analysis will be performed comparing all baseline and follow-up data of completers and dropouts.

In exploratory analyses of all intervention cases, structural equation models will be used, including variables of three dimensions: (1) patient baseline characteristics, (2) CCM treatment procedures as actually carried out and (3) pre-post differences on outcome assessment scores. Through these analyses, we intend to identify possible interactions between characteristics of patients and treatment performance and to deepen our understanding of how the treatment might work and for which patients it can work best.

Cost-effectiveness analyses of LoChro-Care will be carried out from the healthcare perspective. Therefore, the change-from-baseline scores of the WHODAS, PHQ-9 and PACIC will be analysed in relation to the costs of medical resource utilisation and the costs of the work of chronic care managers. Incremental cost-effectiveness ratios and corresponding confidence intervals will be estimated using seemingly unrelated regressions, a multivariate regression technique that accounts for the potential correlation between cost and outcome (score) measurements. Based on data from the FIMA instrument, standardised unit costs will be applied to quantify the costs of medical resource utilisation. With the aim of increasing the precision of the assessment, we will complement the FIMA questionnaire with a prospective diary method in a subsample. Over a 12-month period, patients will be requested to record their medical resource utilisation. The diary is designed as a table including the main aspects of medical costs. Cost-effectiveness analyses will be conducted for the whole sample as well as for the subsample with diary cost assessments in the intervention and control group. In addition, the costs of the work of chronic care managers will be determined. We will consider employers’ labour costs and costs for the administration and coordination of the chronic care managers (lump sum of 25% of personnel costs).

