#### Implementation and time schedule of the intervention

After receiving the contact details, the CCM will arrange an appointment with the patient at the patient’s home for approximately one week after discharge. The assessment of the questionnaires summarised in Table 1 and individual interviews will form the basis to establish an individual care plan, which will be discussed and decided upon with the patient within two weeks after the first contact. The individual care plan consists of one or more of the following steps: (1) If the existing support by the general practitioner and family or other informal caregivers is sufficient, the CCM will compile, explain and deliver an individualised care plan including information about enhanced self-management and about geriatric outpatient services which are relevant and accessible to the patient. The CCM can choose relevant information about regional geriatric services from an internal project database including links to profiles and contacts. The CCM will encourage the patient to communicate the care plan to all informal and formal care partners. (2) If the patient suffers from cognitive impairment, the CCM intervention will involve the primary caregiver. (3) If there is no primary caregiver and other informal support is lacking, the CCM will establish contact with lay helpers who can serve in a supporting role. (4) If contacts with a general practitioner have been too infrequent or non-existent, the CCM will help to establish this provider relationship with adequate frequency of contact. (5) If the medication list reveals uncertainties for the patient or no medication list exists, the CCM will encourage the patient to get in touch with his/her general practitioner to work on medication problems. (6) If further formal care is needed, the CCM will help to contact the general practitioner and to establish contact with local geriatric services. Examples of local services involved are nursing day care, outpatient services, geriatric outpatient rehabilitation, housing agencies or private practices for physiotherapy or occupational therapy as well as further psychosocial facilities. Four weeks after the second contact, all planned steps will be monitored and discussed with the patient at his/her home. If no personal contact is required, the next three contacts will take place through telephone calls, in which the CCM discusses possible needs for care plan changes with the patient. The final “closing” contact will take place 50/51 weeks after baseline at the patient’s home and will consist of reflections on achievements as well as a summary of recommendations for future care. Additional contacts to this standard intervention are possible in the case of depression or diabetes. For depression, six additional contacts (at home and via telephone) will take place, in which patients are trained in problem-solving techniques. This method has proven successful in numerous depression trials [38, 39]. For diabetes as a present condition, three additional contacts at the patient’s home or via telephone are possible. These contacts will include diabetes-related self-management issues. Details about the sequence of intervention sessions can be found in Fig. 2. To ensure treatment fidelity, the CCM will receive regular specialist counselling by a geriatrician and by a study team member of the University of Education.

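### Models fitted to intervention patients alone show who changes, not for whom LoChro-Care works best; that aim needs both randomised arms

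*Protocol article*

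**What the plan says.** The plan is in the second paragraph of Statistical analyses: "In exploratory analyses of all intervention cases, structural equation models will be used, including variables of three dimensions". Two of these dimensions serve as explanatory variables: "1) patient baseline characteristics, (2) CCM treatment procedures as actually carried out". The third is the outcome: "pre-post differences on outcome assessment scores". The authors want to identify possible interactions between patient characteristics and treatment performance, and "to deepen our understanding of how the treatment might work and for which patients it can work best".

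Four other statements bear on this.

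- The same section plans one analysis of effect modification that is described as comparing intervention effects: "Subgroup analysis will be conducted to reveal group differences in intervention effects between patients with serious versus slight health-related strain". The groups are ISAR 3 or more versus below 3.
- Implementation and time schedule of the intervention makes intensity depend on diagnosis: "For depression, six additional contacts (at home and via telephone) will take place". Three further contacts are possible for diabetes.
- Blinding states: "In both groups, patient outcomes will be collected by independent assessors". Table 1 lists WHODAS 2.0 and PHQ-9 at 0, 12 and 18 months for all participants.
- Public dissemination, transfer and implementation says that new hypotheses from the process evaluation need confirmation in further research.

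**The concern.** Asking for which patients a treatment works best means asking whether the difference between LoChro-Care and usual care varies with patient characteristics. The planned models contain no usual-care patients, so that difference is not in their data. A path from a baseline trait to change in treated patients shows who improved. It cannot separate improvement due to LoChro-Care from improvement that would have happened anyway.

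Two mechanisms could pass for differential benefit. First, any prognostic factor predicts change whether or not it modifies the effect. Second, a high T0 score tends to be followed by a lower one, so a baseline score, or anything correlated with it, predicts the change score that contains it. Recruitment favours this: patients come from inpatient and outpatient units, especially the emergency unit, and are selected on an ISAR score of 2 or more.

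The delivered-procedure paths have a related problem. Patients with depression are scheduled for more contacts, and depression is one of the two primary outcome domains. More contacts will therefore tend to go with higher baseline PHQ-9 scores, and hence with larger expected falls.

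At stake is the reading of the process evaluation. It could suggest that the patients who start worst, or who receive most contacts, gain most from the programme when neither is true.

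**Working it through.** **Inputs from the protocol article.** Standardised difference 0.3, one-sided 0.05, 95% power, 20% dropout, 242 per arm assessed at 12 months, 606 randomised (Sample size and power calculation). Contacts: 7 to 16 in total, with six extra for depression and up to three for diabetes.

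**Assumptions, not in the documents.** Baseline-to-follow-up correlation r of 0.5 to 0.8; equal variances at both times; higher scores mean worse.

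**Stated sample size.** The normal approximation gives 241 per arm. The exact noncentral t gives 242 (power 0.9506). Then 242/0.8 = 302.5, so 303 per arm and 606 in total. The stated figure reproduces, and 242 is used below as the number of intervention completers.

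**Regression to the mean.** Let b be the standardised baseline and y the follow-up score, with the same treatment effect for everyone. In the intervention arm:

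- slope of (y - b) on b = r - 1
- corr(b, y - b) = (r - 1)/sqrt(2(1 - r)) = -sqrt((1 - r)/2)

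This gives -0.50 at r = 0.5, -0.447 at 0.6 and -0.387 at 0.7. At n = 242 even -0.387 has Fisher z = atanh(0.387) x sqrt(239) = 0.408 x 15.46 = 6.3.

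**Simulation.** 2,000 trials for each r, 242 per arm, constant effect of 0.3 SD, no effect modification, two-sided 5% tests:

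| r | Intervention arm only: slope of change on baseline | Significant | Both arms: mean arm-by-baseline interaction | Significant |
|---|---|---|---|---|
| 0.5 | -0.50 | 100% | 0.00 | 4.3% |
| 0.6 | -0.40 | 100% | 0.00 | 6.0% |
| 0.7 | -0.30 | 100% | 0.00 | 4.7% |
| 0.8 | -0.20 | 100% | 0.00 | 5.5% |

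**A purely prognostic factor.** A variable unrelated to baseline that shifts change by 0.2 SD per SD equally in both arms (assumed strength) was significant in the intervention-only analysis in 86%, 93%, 98% and 99.9% of trials as r rose from 0.5 to 0.8. It modifies nothing.

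**Contact number.** 7 + 6 + 3 = 16, so the two diagnoses account for the whole stated range. Suppose the six extra contacts go to patients with b above +0.5 SD (assumed cut-off) and have no effect of their own. The gap in mean baseline between the two groups is 0.352/0.309 + 0.352/0.691 = 1.65 SD, and the gap in mean change is 1.65 x (r - 1): -0.83, -0.66, -0.50 and -0.33 SD for r = 0.5 to 0.8. The simulation gave -0.83, -0.66, -0.49 and -0.33, significant in 97% to 100% of trials.

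**Change score or follow-up score?** If b is in the model, y - b = a + βb + γx is the same equation as y = a + (β + 1)b + γx, and γ is unchanged. Replacing the change score removes the artefact only from the baseline path. It does not turn γ into effect modification; only the control arm can.

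**The case against.** The strongest defence is that this is a process model. Delivered care-manager procedures exist only in the intervention arm, so the aim of relating patient characteristics to treatment performance cannot be pursued in controls. The protocol calls the analysis exploratory, words its aim cautiously, and asks for confirmation of new hypotheses. All of this stands: an intervention-only model is legitimate for describing delivery. It does not rescue the remaining aim. An exploratory label covers uncertainty and multiplicity, whereas here the contrast does not contain the quantity sought and the error has a predictable direction.

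It can also be said that the correlations above presuppose a specification the article does not give, since it does not name the baseline characteristics. That is right. The figures apply if the baseline score of the same outcome is a predictor, and correlates of it carry only part of the artefact. Likewise, baseline characteristics are already one dimension of the model, so adjusting dose paths for depression and diabetes fits the plan. The confounding applies to unadjusted paths.

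A reader might infer three stronger things that the documents do not support. One is that these models feed the best-practice guideline and so steer care managers; the dissemination section bases that guideline on appraisal of care plans and profiles of local services, and does not mention the models. Another is that no controlled look at effect modification is planned; the ISAR subgroup analysis is one, though for a single dichotomised variable. The third is that every patient is assessed around an acute event; outpatient units recruit too.

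**Conclusion.** The point holds, limited to one stated purpose of an exploratory analysis. Models restricted to intervention patients identify predictors of change. They cannot identify the patients for whom LoChro-Care works best. With no effect modification at all, baseline correlates with change at -0.50 to -0.39 for r = 0.5 to 0.7, and the one-arm slope was significant in every simulated trial, against about 5% for the two-arm interaction. The sizes rest on the assumed r, equal variances, the assumed prognostic strength and the assumed dose cut-off. With equal variances, the direction of the baseline artefact holds for any r below 1.

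This is not a threat to the trial's main result: the comparison of randomised arms on the primary outcomes does not use these models. It is more than an omitted detail, because the article itself states the analysis set, the outcome and the aim, and the three do not fit together.

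**What to change.** 1. Move the question of who benefits most into both randomised arms. For each candidate modifier, fit the follow-up score on arm, baseline score, modifier and arm-by-modifier interaction, as an exploratory extension of the ISAR subgroup analysis. Use variables available for everyone, such as WHODAS, PHQ-9, ISAR score, age, sex and diagnoses; the section on additional evaluation names most of these as matching variables for control cases. Measures that Table 1 gives only for the first care-manager session, such as MMSE and SPPB, cannot serve, because controls lack them.
2. Keep the intervention-only model, describe it as covering delivery and predictors of change, and remove "how the treatment might work and for which patients it can work best" from its purpose.
3. Condition paths from contact number to outcome on depression and diabetes status. Since these diagnoses account for the planned range, what remains is largely departure from the planned number, and those paths should be read accordingly.

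The cost is a modest amount of extra exploratory analysis and no new data. Power will be limited. For a standardised modifier with 242 per arm, the interaction has standard error sqrt(2(1 - r²)/242), which is 0.079 at r = 0.5 and 0.065 at r = 0.7. For 80% power at two-sided 5% the interaction must be about 2.8 times that, or 0.22 to 0.18 SD per SD, against an assumed overall effect of 0.3 SD. Estimates should be reported with confidence intervals and read as hypotheses.

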## Methods/design

### Trial design/setting

The present study will be conducted within the routine care context and is designed as a prospective, two-group usual care controlled trial with 1:1 randomisation on the participant level. Participants will be recruited from all for geriatric patients relevant inpatient and outpatient units of the Medical Center – University of Freiburg, especially the emergency unit. During the 18-month observation period, the chosen endpoints will be measured three times (at baseline, after 12 months and after 18 months). Participants in the intervention group will be supported by a chronic care manager (CCM) over a period of 12 months. The study will be implemented according to CONSORT guidelines (see Fig. 1).

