
**Table 1 Tab1:** LoChro outcome measures, instruments, and times of assessment

Time of assessment (months)	T_0_ (0)	CCM-session 1	T_1_ (12)	T_2_ (18)
Primary outcome				
Functional health (WHODAS 2.0)	X		X	X
Depression (PHQ-9)	X		X	X
Secondary outcomes				
Satisfaction with care (PACIC)	X		X	X
Ressource utilisation (FIMA)	X		X	X
STOPP/START criteria	X		X	X
Health-related quality of life*	X		X	X
Satisfaction with life (Kurzskala L-1)	X		X	X
Intervention group only				
Daily Functioning (Barthel-Index)		X		
Daily Functioning (IADL)		X		
Cognition (MMSE)		X		
Mood (PHQ-9)		X		
Alcohol Use (Audit C)		X		
Mobility (SPPB)		X		
Medication Management*		X		
Individual Interview on patient’s preferences and care situation*		X		

AUDIT-C: Alcohol Use Disorders Identification Test-Consumption; Barthel-Index: daily functioning in older people; FIMA: Fragebogen zur Erhebung von Gesundheitsleistungen im Alter; IADL: Instrumental Activities of Daily Living; Kurzskala L-1: single item scale on satisfaction with life; MMSE: Mini-Mental-State-Examination; PACIC: Patient Assessment of Chronic Illness Care; PHQ-9: Patient Health Questionnaire; SPPB: Short Physical Performance Battery; Stopp/Start: Stopp/Start criteria for potentially inappropriate prescribing in older people; WHODAS 2.0: World Health Organization Disability Assessment Schedule 2.0; *: self-constructed items

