#### Sample size and power calculation

Based on dropout rates of about 20% in our previous studies and small effects of case and care management on functional health, we hypothesise a Standard Mean Difference of 0.3 to be detected. We calculated a sample size of 606 persons to be randomised at baseline and 242 patients in each arm to be assessed at 12 months (one-sided t-test, significance level 0.05, 95% power, computed for per-protocol analysis, assumption 20% dropout at month 12).

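### The cost-effectiveness analysis names change-from-baseline scores as the effect measure without a baseline covariate, which gives up precision that could be had at no cost

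*Protocol article*

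**What the plan says.** The section Statistical analyses of the protocol article treats the scores in two places.

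- **Clinical analysis.** The outcome scores are the dependent variables, and baseline is handled by "adjusting for baseline group differences (independent variables").
- **Cost-effectiveness analysis.** The effect measure is fixed: "the change-from-baseline scores of the WHODAS, PHQ-9 and PACIC will be analysed in relation to the costs of medical resource utilisation", together with the cost of the care managers' work. Incremental cost-effectiveness ratios and their confidence intervals are to come from "seemingly unrelated regressions, a multivariate regression technique that accounts for the potential correlation between cost and outcome (score) measurements". No covariates are listed and none are ruled out. The analysis is run in the whole sample and again in a subsample that keeps a cost diary.

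Table 1 shows that WHODAS, PHQ-9, PACIC and FIMA are all collected at baseline, 12 months and 18 months. They stand outside its block of instruments used in the intervention group only, so baseline values exist in both arms.

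**The concern.** Subtracting the baseline score is not the same as adjusting for it. A change score fixes the slope of follow-up on baseline at 1. When the correlation between the two is below 1 and the SDs are similar, that slope is too steep, and the difference between arms carries baseline noise that a regression on baseline would remove.

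The effect is the denominator of the incremental cost-effectiveness ratio. Ratios and their intervals become unstable as the denominator nears zero, and the sample size section itself expects only small effects. Baseline scores are balanced by chance alone, since "Block randomisation will be used with no stratification". In the diary subsample, which is smaller, chance imbalance will be larger.

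**Working it through.** **Inputs.** From the protocol article: "1:1 randomisation on the participant level" (Trial design/setting); "we hypothesise a Standard Mean Difference of 0.3 to be detected" and "one-sided t-test, significance level 0.05, 95% power, computed for per-protocol analysis, assumption 20% dropout at month 12" (Sample size and power calculation); 242 per arm assessed at 12 months and 606 randomised (same section). Assumed: a baseline-to-follow-up correlation rho of 0.3 to 0.8, which the document does not give; equal SD at both times, set to 1; the same rho in both arms.

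**The plan's own figure.** With a difference of 0.3 SD, one-sided 0.05 and 95% power, the exact t-test needs 242 per arm (power 0.9506). Allowing for 20% dropout, 242 / 0.8 = 302.5, so 303 per arm and 606 in all. The stated sample size reproduces. No figure is stated for the economic analysis, so 242 per arm is used below.

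**Precision.** For one patient:

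- change score without baseline covariate: 1 + 1 − 2·rho = 2(1 − rho)
- baseline-adjusted: 1 − rho² = (1 − rho)(1 + rho)
- ratio, adjusted to change: (1 + rho)/2, below 1 for every rho below 1

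The standard error of the difference between arms is √(2v/242), with v the variance above.

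**Chance imbalance.** If the arms differ by d SD at baseline, the unadjusted change-score difference shifts by −(1 − rho)·d. One standard error of the baseline difference is √(2/242) = 0.091 SD.

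| rho | v, change | v, adjusted | ratio | SE, change | SE, adjusted | size of shift for d = 0.091 |
|---|---|---|---|---|---|---|
| 0.3 | 1.40 | 0.91 | 0.65 | 0.108 | 0.087 | 0.064 |
| 0.5 | 1.00 | 0.75 | 0.75 | 0.091 | 0.079 | 0.045 |
| 0.6 | 0.80 | 0.64 | 0.80 | 0.081 | 0.073 | 0.036 |
| 0.8 | 0.40 | 0.36 | 0.90 | 0.058 | 0.055 | 0.018 |

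The SE of the change score is larger by the factor √(2/(1 + rho)): 20% at rho 0.4, 8% at 0.7, 5% at 0.8. Below rho 0.5, 2(1 − rho) exceeds 1, and the unadjusted change score is noisier than the follow-up score with baseline ignored.

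**Change score with its baseline as covariate.** Let Y be follow-up, B baseline and G arm. If Y − B = a + t·G + k·B + error, then Y = a + t·G + (k + 1)·B + error. The treatment coefficient t and the residuals are the same; only the coefficient of B moves by 1.

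**Simulation.** Seemingly unrelated regressions were run with 242 per arm, a true effect of −0.3 and 2,000 runs at each of rho 0.4 and 0.6.

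- The unadjusted change score averaged −0.299 and −0.298, so it is unbiased.
- Its empirical SD was 0.098 and 0.082, against 0.082 and 0.074 with baseline in the outcome equation.
- Its estimate correlated −0.55 and −0.45 with the baseline imbalance.
- With baseline as covariate, change and follow-up outcomes agreed in every run (largest difference 8 × 10⁻¹⁵).

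**The case against.** The strongest reply is that the article never calls the change scores raw or unadjusted. A seemingly unrelated regression can carry the baseline score, and if it does, the loss is zero. The covariate list of a secondary economic model may well stand in a fuller document, and the baseline adjustment stated for the clinical analysis is not revoked. This stands as far as it goes: a reader might infer that the plan rules out adjustment or contradicts itself, and the text supports neither. It does not dispose of the point. The article fixes the effect measure, states baseline adjustment for one analysis and not for the other, and an analyst who follows the text alone would run the less precise model.

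Three further inferences are tempting and do not hold.

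- **Bias.** With 1:1 randomisation, regression to the mean after a hospital contact acts on both arms, and the unadjusted estimate is unbiased on average. The shift from imbalance is chance error already contained in the larger standard error, not a second harm.
- **Conflict with the main result.** The main analysis uses a composite of z-scored WHODAS and PHQ-9; the economic analysis takes WHODAS, PHQ-9 and PACIC. These effects would differ under any adjustment.
- **Costs as change scores.** The article does not say that costs are analysed as change from baseline, so there is no error to correct in the cost equation.

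It is also fair to say that the effect on the interval for the ratio cannot be sized, because the document gives no cost variance.

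**Conclusion.** The point holds as a free improvement to a stated analysis choice. Run with change scores and no baseline covariate, the effect estimate is unbiased on average but less precise than a baseline-adjusted one. The adjusted variance is 65% of the change-score variance at rho 0.3 and 90% at rho 0.8, which on the effect side is like giving up 35% to 10% of the patients. A one-standard-error baseline imbalance moves the unadjusted estimate by 0.06 to 0.02 SD over the same range, beside a planned effect of 0.3 SD.

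These figures rest on the assumed rho, on equal SDs and on 242 per arm. They fall to zero if the baseline score is in the outcome equation. The point touches the secondary economic analysis only; the primary test and the sample size are not affected.

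**What to change.** State in the economic analysis that each outcome equation of the seemingly unrelated regressions includes the baseline value of its own score (WHODAS, PHQ-9 or PACIC) as a covariate beside arm, in the whole sample and in the diary subsample. The outcome may stay the change score or become the follow-up score, since the treatment estimate is the same. Baseline cost from FIMA may be added to the cost equation as an option.

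The cost is one sentence. All the variables are already collected at baseline in both arms.
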